#### Phase 4: Evaluating Outcomes and Disseminating Results to Stakeholders

An exploratory mixed methods approach will be used to evaluate implementation outcomes. Initially, feedback from qualitative interviews will be prioritized since qualitative interviews yield rich data and allow flexibility to probe deeply on specific issues. The first 20 clients to use the digital platform to inform their stratification of care will be approached for qualitative interviews. We will ask clients about their satisfaction with the PROMs and stratified care systems, what factors they felt influenced the stratification decision, the extent to which they agreed with the stratification decision, as well as probe for barriers and facilitators to the use of PROMs and stratified care.

Once 100 clients have been enrolled in the study for at least 3 months (meaning they have received their initial clinical stratification and at least one treatment review), we will begin to use quantitative data to evaluate outcomes of the stratified care process. Based on current rates of onboarding described earlier, we estimate that we will reach this target sample size in approximately 1 year. We will examine the stratum a client is assigned to and map the trajectory of symptoms and satisfaction with clinical services (see instruments in Table 3). Statistical regression models will be developed to describe symptom change over time and determine whether symptom trajectory (eg, slope of regression model) is modified by stratum of care when controlling for other variables (eg, demographics and social determinants of health).

Clients and their clinicians will have access to the data provided by the client to inform future treatment decisions. The research team will present their interim analysis of the results to the clinical team at team meetings at least once every 3 months. One year after recruitment begins, the research team will conduct focus groups and interviews with clinicians and managers at the study site to understand their satisfaction with PROMs and stratified care, barriers and facilitators to the use of PROMs and stratified care, and the factors that influence their decisions about clinical stratification.

**Table 3 table3:** Data collection using RE-AIM (Reach, Effectiveness, Adoption, Implementation, and Maintenance) framework.

RE-AIM category and data source		Items

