#### Phase 2: Designing an Initial Stratified Care Model

Prior to the implementation of an RLHS, standard care at the study clinic was to have clients work with their assigned clinician to select appropriate treatments from among the available options at the clinic. Coincident with the implementation of an RLHS, the clinic made an operational decision to move to a stratified care model, whereby new clients would be appropriately matched to different intensities of care. The optimal timing for PROMs was identified within the clinical workflow: specifically, after a client had received their orientation to the clinic, but before they were assigned to a primary clinician. Managers and clinicians at the study site engaged in multiple rounds of discussion, feedback, and revisions to organize both existing and new services into different strata of care. The initial model includes 3 strata of care (low, medium, and high, which are known in the clinic as “yellow,” “blue,” and “purple,” respectively). Some services are only available to clients in each stratum, while other services are available to all clients regardless of stratum (Figure 3).

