#### Phase 3: Combining Implementation of PROMs With Stratified Care

After selecting and implementing a digital platform for the delivery of PROMs and a stratified care model, the next phase was to identify how to use the platform to guide stratification within the study clinic. This involves engaging in rapid learning cycles as the Innowell system was created with a population-wide focus, but the study site serves a much narrower population of emerging adults with moderate to severe mental health concerns. Further, given the clinic-specific stratified care model implemented, further learning cycles were required to determine how to use the results from the selected platform to assign a stratum of care. To accomplish this, at the study site, new clients who consent are onboarded to the Innowell platform and asked to complete all 20 domains available on the platform. In the last 9 months, we introduced the Innowell platform and successfully onboarded 56 clients. Uptake has increased during this time, and at the time of writing, we were onboarding an average of 9 emerging adults per month. Managers and clinicians participate in weekly case conferences where individual clients’ results, referral information, and case history are presented and discussed. Consensus-based decision-making is used to determine the initial client stratum. A researcher will be present during each case conference to capture notes regarding the decision-making process including the key findings used to determine stratum and level of agreement among team members.

As per the stratified model of care, clients will meet with their clinician every 3 months to review treatment progress including current results from readministering all 20 domains. Treatment reviews will be used to determine if clients should be moved to a different stratum of care, transferred to another program, or discharged from the health system. After each clinical stratification treatment review, clients will complete a custom form to provide their feedback on the treatment review and clinical stratification process. We will also conduct a detailed chart review to understand the impact of implementing standardized PROMs and stratified care on the services clients use at the study clinic as well as their use of wider health system resources. This chart review will also include clients who did not consent to research if a waiver of consent can be obtained.

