### Data Analysis

We will use the RE-AIM framework to design and organize the data collection system (Table 3). The *Reach* dimension captures individual outcomes and includes the proportion of stakeholders who take part in the research, complete quantitative and qualitative assessments, and use the additional care options, apps, and e-tools on the Innowell platform. The *Effectiveness* domain also examines individual outcomes and measures changes over time in key outcomes related to mental health (among youth clients), satisfaction with PROMs and stratified care (among clients and clinicians), as well as the use of health care resources (from administrative data). *Adoption* and *Implementation* measure organizational outcomes and so will be more important in later phases of the research when examining how many clinics adopt PROMs and stratified care as well as what are the barriers and facilitators to adoption. *Maintenance* has the longest timescale among RE-AIM dimensions, and it will be used to measure the sustainability of implementation of PROMs and stratified care over time at an organizational and individual level.

This study will begin at the same time as the clinic is implementing stratified care for all clients. For clients who consent to research, PROM results will be used to help inform stratified care, whereas nonresearch participants will be stratified based on clinical judgment alone. The impact of stratified care and implementing PROMs will be inferred from longitudinal changes in client and clinic data, although we cannot control for the impact of other variables changing over time. We will seek a waiver of consent to compare research participants to nonresearch participants, which will provide more direct insights into the impact of using PROMs to inform a stratified care model of mental health service delivery. Analysis will be guided by the three key objectives.

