Improving treatment selection: We will examine changes over time in symptoms for clients at the study clinic. To the extent that implementation of PROMs is leading to continuous improvements in treatment selection as part of an RLHS, we would expect that participants enrolled at the beginning of the study will show slower improvements in their mental health relative to clients enrolled later in the study (as measured by instruments in Table 1). Additionally, if a waiver of consent can be obtained to compare research participants to nonresearch participants, we expect that research participants will show greater improvements in mental health than nonresearch participants when controlling for clinic intake date.Reducing average wait time (prior to service) and treatment duration (once in service): We will examine clinic administrative data to understand whether the implementation of PROMs and stratified care leads to reductions in wait time and treatment duration. If we can obtain a waiver of consent, we will examine whether research participants (completing PROMs using the Innowell platform) spend less time in treatment than those who opt out of research (and do not complete PROMs using the Innowell platform).Increasing the value of services: Clinic administrative data will be used to understand the cost of providing care to each client. When combined with data derived from PROMs, this will provide information about the degree of symptom improvement associated with each type of service. If we can obtain a waiver of consent, we will be able to determine whether the average cost of providing care to a client changes when informed by PROMs. The clinic also seeks to understand the value of services provided to increase cost-effectiveness. By tracking client outcomes associated with each treatment, we can identify which services provide the greatest return on investment.

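### Stratum is set partly from the baseline score that starts the symptom slope, so the slope-by-stratum test and the return-on-investment claim can support description only

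*Protocol article*

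**What the plan says.** The protocol article describes assignment and analysis in four places.

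- **Timing (Phase 2).** PROMs are completed "after a client had received their orientation to the clinic, but before they were assigned to a primary clinician".
- **Assignment (Phase 3 and Data Analysis).** At weekly case conferences individual clients' "results, referral information, and case history are presented and discussed", and "Consensus-based decision-making is used to determine the initial client stratum". Data Analysis confirms the role of the scores: "For clients who consent to research, PROM results will be used to help inform stratified care". The Introduction explains that in stratified care more severe illness receives more intensive treatment from the start. Stratum is revisited every 3 months: "Treatment reviews will be used to determine if clients should be moved to a different stratum of care".
- **Model (Phase 4).** Once 100 clients have been in the study for at least 3 months, regression models will determine whether the slope of symptoms over time "is modified by stratum of care when controlling for other variables (eg, demographics and social determinants of health".
- **Services (Phase 2 and Data Analysis, third objective).** "Some services are only available to clients in each stratum", while others are open to everyone. By tracking outcomes for each treatment, the article says, "we can identify which services provide the greatest return on investment".

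The limitations it names are other factors changing over time (Data Analysis) and selection by consent (Potential Challenges and Limitations). Neither concerns assignment by severity.

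**The concern.** A client whose baseline score is high partly by chance is more likely to be placed in a higher stratum, and the next score will tend to fall whatever care is given. Because the baseline score is also the first outcome value, this fall enters the stratum-by-time term. The covariates named as examples do not remove it.

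Referral and history information adds a second problem. It helps set the stratum and may itself predict outcome, which is confounding by indication. Services tied to a stratum inherit both problems. For services open to all strata, no allocation independent of client need is described.

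At stake is what the study may conclude. Phase 4 sets out to determine effect modification, and the third objective claims to identify the best-value services. Interim results go to the clinical team at least every 3 months, and the decision tree and the services in each stratum are periodically re-examined.

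**Working it through.** The article gives no reliability, assignment weight, power or effect size, and 100 is a trigger for analysis rather than a powered sample size. There is thus no figure to reproduce. The check asks how large a stratum difference appears when none exists.

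**Inputs.** From the article: 100 clients, three strata, and assignment from PROM plus chart information. Assumed: strata are thirds of a severity judgment; the reliability of the PROM score, *r*, is 0.6 to 0.8; true severity is stable; chart information *C* reflects true severity with reliability *c* of 0.5 to 0.8. Scores are in SD units and higher is worse. With two visits, the slope is the change score.

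**Formula.** Let the judgment be S = w·Y0 + (1 − w)·C, where Y0 is the baseline PROM and w its weight. Then

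- SD(S) = √[w² + (1 − w)² + 2w(1 − w)√(rc)]
- expected high-minus-low difference in change = −k·w(1 − r)/SD(S)
- k is the gap between the means of the top and bottom thirds of a normal variable: 2 × 3 × 0.3636 = 2.18

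**Numbers put in.**

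- w = 1: 2.18 × 0.2 = 0.44 (r = 0.8) and 2.18 × 0.4 = 0.87 (r = 0.6).
- w = 0.5: r = c = 0.8 gives SD(S) = √0.90 = 0.949, so 2.18 × 0.5 × 0.2/0.949 = 0.23. With r = 0.6 and c = 0.5, SD(S) = √0.774 = 0.880, so 2.18 × 0.5 × 0.4/0.880 = 0.50.
- w = 0.3: the same steps give 0.14 and 0.29.
- w = 0: zero.

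**Simulation with no stratum effect** (3,000 runs per cell, top versus bottom third, two-sided test at 5%; ranges over *r* and *c*):

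| PROM weight | Unadjusted difference, SD | False positives | After baseline-PROM adjustment, SD | False positives |
|---|---|---|---|---|
| 1 | −0.44 to −0.87 | 81%–99% | about 0 | about 5% |
| 0.5 | −0.23 to −0.50 | 31%–63% | +0.36 to +0.85 | 27%–64% |
| 0.3 | −0.14 to −0.29 | 14%–26% | +0.39 to +0.93 | 39%–83% |
| 0 | 0 | about 5% | +0.39 to +0.92 | 53%–94% |

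A negative value means the high stratum falsely appears to improve more; a positive value means it falsely appears to do worse. Where PROM and chart both decide, adding *C* beside the baseline score brought the difference back to about 0 and the error rate to about 5%.

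**Check with fitted slopes.** Individual least-squares slopes were compared across three strata with a 2-df F test (2,000 runs, reliability 0.6 to 0.9). With visits at 0, 6 and 12 months and the PROM alone deciding, the false difference was −0.22 to −0.86 SD per 12 months, with 42% to 97% false positives. With PROM weight 0.7 and chart information unrelated to outcome, false positives were 16% to 71% over all visit schedules tried.

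If chart information also predicts the slope (assumed 0.3 SD per 12 months per SD; reliability 0.8; PROM weight 0.7; visits at 0, 3, 6 and 12 months), the unadjusted difference is +0.22 with 21% false positives. After baseline adjustment it is +0.75 with 94%.

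The simulations cover the stratum comparison. The point about services follows by reasoning and was not simulated.

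**The case against.** The strongest objection is to the obvious remedy. Adjusting for baseline PROM scores works only if the rest of the assignment judgment is unrelated to prognosis, and referral and history information is unlikely to be. The table bears this out: where chart information dominates, PROM-only adjustment is worse than the planned analysis. This stands and shapes the fix.

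Second, the covariate list is given by way of example, the models are still to be developed, the approach is called exploratory, and an article leaves detail to an analysis plan. Baseline severity is not excluded. That is fair, but adding it as a main effect would not repair a stratum-by-time term, and the stated aims go beyond exploration.

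Stronger readings are tempting, and the documents do not support them:

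- *Current stratum will be the exposure.* Phase 4 speaks of the stratum a client is assigned to, and Table 3 lists the number and timing of stratum changes as a separate item. The risk arises only if later moves are allowed to redefine the exposure.
- *The high stratum is bound to look better.* Prognostic chart information can reverse the direction.
- *Services will be ranked across strata.* No such model is specified, and some services are open to all. The fault is the causal claim.
- *The artefact will automatically change care.* Phase 5 builds the decision tree from case-conference notes and adapts it at joint meetings. No rule ties a regression result to a change.

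**Conclusion.** The concern holds in this form: as described, the slope-by-stratum test cannot separate a stratum effect from regression to the mean and confounding by indication, and the return-on-investment claim is open to the same confounding. The mechanism follows from the article's own assignment process.

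The size rests on assumptions. At reliability 0.6 to 0.8, false positives run from about 15% to over 80% as the weight on the PROM rises, and reach the nominal rate only when that weight is zero. Neither the direction of the bias nor its removal by baseline adjustment can be taken for granted. A map of trajectories by stratum remains sound as description.

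**What to change.** 1. **Exposure.** In Phase 4, state that the exposure is the initial stratum as first assigned, and report later moves separately.
2. **Model.** Analyse post-baseline scores conditional on the baseline score of the same scale, or let baseline modify the slope. Add a short list of the key findings that the researcher already records at each case conference, including referral and history items and not PROM scores alone. With 100 clients in three strata, all 20 domains cannot be carried. Show the result beside the unadjusted slopes, so that readers see how far it depends on adjustment.
3. **Interpretation.** State in Phase 4 and in Data Analysis that stratum and service differences are descriptive and confounded by indication, and add this to the limitations.
4. **Third objective.** Replace the return-on-investment claim with a descriptive, severity-adjusted summary of cost and outcome among services available to the same stratum.

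**Cost.** The change is mainly wording, made before the 100-client analysis, plus coding of conference notes that are already planned. The causal cross-stratum and return-on-investment conclusions are given up. Residual confounding remains: the simulated recovery assumed that all chart information behind the decision was available to the model, and conference notes will not capture it all.

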**Reach (individual)**		
	Clients	The proportion of clients who participate in a research study, complete quantitative surveys, take part in qualitative interviews, and use extra support resources in Innowell platform
	Clinicians	The proportion of clinicians who complete training on using PROMs^a^, participate in a research study, complete quantitative surveys, and take part in qualitative interviews
	Managers	The proportion of managers who complete training on using PROMs, participate in a research study, and take part in qualitative interviews
**Effectiveness (individual)**		
	Admin data (health region)	The proportion of clients who (for psychiatric reasons) visit urgent care center, who visit emergency department, and who are hospitalized
	Admin data (clinic)	Change over time in the proportion of clients assigned to each stratum of care, the proportion of clients who drop out of treatment, length of waitlist, time spent in the program, cost of services used, number of sessions used, type of services accessed, and number and timing of strata changes
	Clients	Change over time in answers to quantitative surveys, reasons for dropping out of research or treatment, confidence managing mental health services, satisfaction with mental health services and care coordination, satisfaction with the use of PROMs and stratified care, individual barriers and facilitators to the use of PROMs and stratified care, and agreement with clinician and data derived from PROMs regarding stratified of care assignment
	Clinicians	Change over time in answers to quantitative surveys, satisfaction with the use of PROMs and stratified care, individual barriers and facilitators to the use of PROMs and stratified care, and agreement with client and data derived from PROMs regarding stratum of care assignment
	Managers	Change over time in satisfaction with the use of PROMs and stratified care and individual barriers and facilitators to the use of PROMs and stratified care
**Adoption (organizational)**		
	Clinics, clients, clinicians, managers	The proportion of clinics that adopt PROMs and stratified care and stakeholders within clinics (clients, clinicians, and managers) who take part in the implementation of PROMs and stratified care
**Implementation (organizational)**		
	Clinics, clients, clinicians, managers	Organizational barriers and facilitators to the implementation of PROMs and stratified care and changes to the use of PROMs and stratified care relative to the intended use
**Maintenance (individual and organizational)**		
	Clinicians, managers, executive leaders	Commitment to continuing using PROMs and stratified care beyond the study period and spread and scale of PROMs and stratified care

^a^PROM: patient-reported outcome measure.

#### Phase 5: Modification of Stratified Care Based on Data Derived From PROMs

Initially, the clinical team will make rapid changes to both the services offered within each stratum of care and the way dashboards displaying data from PROMs are interpreted and used to match clients into a stratum of care. This pilot phase will be used to ensure managers and clinicians can use early learnings to make effective and efficient changes. Once the management and clinical team report that early learnings have plateaued, planned for 3 months into implementation, the team will use the researcher’s summary analysis of case notes from each case conference to create a decision tree to assign patients to appropriate clinical interventions using the stratified care model developed by the clinical team. As an added step before acting upon the decision tree, every 3 months the research and clinical team will meet to examine the data that have been generated and try to understand how they can adapt the decision tree to increase the precision of using data derived from PROMs to assign a client to a stratum of care. The clinical services available in each stratum will also be re-evaluated.

#### Phase 6: Spread and Scale to New Sites

Initially, this research will be conducted at a single clinic to maximize feasibility and allow for careful evaluation of the use of the stratified care model and its integration with the digital PROM platform.

### Data Analysis

We will use the RE-AIM framework to design and organize the data collection system (Table 3). The *Reach* dimension captures individual outcomes and includes the proportion of stakeholders who take part in the research, complete quantitative and qualitative assessments, and use the additional care options, apps, and e-tools on the Innowell platform. The *Effectiveness* domain also examines individual outcomes and measures changes over time in key outcomes related to mental health (among youth clients), satisfaction with PROMs and stratified care (among clients and clinicians), as well as the use of health care resources (from administrative data). *Adoption* and *Implementation* measure organizational outcomes and so will be more important in later phases of the research when examining how many clinics adopt PROMs and stratified care as well as what are the barriers and facilitators to adoption. *Maintenance* has the longest timescale among RE-AIM dimensions, and it will be used to measure the sustainability of implementation of PROMs and stratified care over time at an organizational and individual level.

This study will begin at the same time as the clinic is implementing stratified care for all clients. For clients who consent to research, PROM results will be used to help inform stratified care, whereas nonresearch participants will be stratified based on clinical judgment alone. The impact of stratified care and implementing PROMs will be inferred from longitudinal changes in client and clinic data, although we cannot control for the impact of other variables changing over time. We will seek a waiver of consent to compare research participants to nonresearch participants, which will provide more direct insights into the impact of using PROMs to inform a stratified care model of mental health service delivery. Analysis will be guided by the three key objectives.

Improving treatment selection: We will examine changes over time in symptoms for clients at the study clinic. To the extent that implementation of PROMs is leading to continuous improvements in treatment selection as part of an RLHS, we would expect that participants enrolled at the beginning of the study will show slower improvements in their mental health relative to clients enrolled later in the study (as measured by instruments in Table 1). Additionally, if a waiver of consent can be obtained to compare research participants to nonresearch participants, we expect that research participants will show greater improvements in mental health than nonresearch participants when controlling for clinic intake date.Reducing average wait time (prior to service) and treatment duration (once in service): We will examine clinic administrative data to understand whether the implementation of PROMs and stratified care leads to reductions in wait time and treatment duration. If we can obtain a waiver of consent, we will examine whether research participants (completing PROMs using the Innowell platform) spend less time in treatment than those who opt out of research (and do not complete PROMs using the Innowell platform).Increasing the value of services: Clinic administrative data will be used to understand the cost of providing care to each client. When combined with data derived from PROMs, this will provide information about the degree of symptom improvement associated with each type of service. If we can obtain a waiver of consent, we will be able to determine whether the average cost of providing care to a client changes when informed by PROMs. The clinic also seeks to understand the value of services provided to increase cost-effectiveness. By tracking client outcomes associated with each treatment, we can identify which services provide the greatest return on investment.

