**Figure 2 figure2:**
[figure not shown]
Dashboard for Innowell software used in patient-reported outcome measures among emerging adults to assess disease severity.

**Table 1 table1:** Standardized measures collected from clients. All instruments are administered at baseline, 6 months, and 12 months using the Innowell platform, except for the Outcome Rating Scale and Session Rating Scale, which are collected after each treatment session using the Research Electronic Data Capture (REDCap) platform.

Instruments	Domains
Kessler Psychological Distress Scale	Psychological distress
Overall Anxiety Severity and Impairment Scale	Anxiety
Quick Inventory of Depressive Symptomology	Depressed mood
Prodromal Questionnaire	Psychosis-like experiences
Altman Self-Rating Mania Scale	Mania-like experiences
Primary Care PTSD^a^ Screen for DSM-5^b^	Posttraumatic stress
Eating Disorder Examination	Eating behaviors and body image
Suicidal Ideation Attributes Scale; Columbia Suicide Severity Rating Scale	Suicidal thoughts and behaviors
Brief Non-Suicidal Self-Injury Assessment Tool	Self-harm
Alcohol, Smoking and Substance Involvement Screening Test; AUDIT^c^ Alcohol Consumption Questions	Alcohol, tobacco, and cannabis use
OECD^d^ Youth not in Education or Employment; WHO^e^ Disability Assessment Schedule; Work and Social Adjustment Scale	Social and occupational function
Schuster’s Social Support Scale	Social connectedness
Pittsburgh Sleep Quality Index; Munich Chronotype Questionnaire	Sleep-wake cycle
Child and Youth Resilience Measure—Revised	Resilience
Multigroup Ethnic Identity Measure	Cultural connectedness
Spiritual Health and Life-Orientation Measure	Spirituality
Inventory of Complicated Grief	Grief and loss
Height, weight, and waist circumference; International Physical Activity Questionnaire	Physical health
Outcome Rating Scale	Overall well-being
Session Rating Scale	Treatment session satisfaction

^a^PTSD: posttraumatic stress disorder.

^b^DSM-5: *Diagnostic and Statistical Manual of Mental Disorders, Fifth Edition*.

^c^AUDIT: Alcohol Use Disorders Identification Test.

^d^OECD: Organization for Economic Co-operation and Development.

^e^WHO: World Health Organization.

**Table 2 table2:** Standardized measures collected from clinicians to assess feasibility and satisfaction with the use of patient-reported outcome measures. All instruments are administered at baseline, 6 months, and 12 months using the Research Electronic Data Capture (REDCap) platform.

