## Discussion

### Principal Findings

This protocol paper describes how we will evaluate the implementation of an RLHS to improve service delivery within a stratified model of care. The study clinic is looking for ways to target the right service to the right client at the right time, in line with current movements toward a precision mental health care system [20]. However, standard care at the study clinic has historically been similar to mental health care in most areas of the world, in that, treatment progress is not systematically tracked using objective measures for most clients [19]. Thus, even if the clinic implemented stratified care as a means to tailor services to client needs, the clinic would have no way of knowing if the stratified care model resulted in improved outcomes. Therefore, the clinic needed to develop a platform for PROMs to monitor outcomes to understand the impact of their new stratified care model. Using PROMs to inform stratified care is challenging since there are no existing guidelines to help clinicians understand how scores on different standardized measures translate into treatment recommendations. Therefore, the clinic will need to use an RLHS framework to guide the use of PROMs in informing stratified care decision-making. Initially, stratification using data derived from PROMs (in combination with clinical judgment) may not be superior to stratification using clinical judgment alone. However, as data are collected on how stratification and treatment selection impact the trajectory of a client’s symptoms, the goal is to iteratively improve the ability to stratify clients and select the best treatment plan.

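### The conditional comparison of mental health improvement between research and nonresearch clients has no repeated symptom measure for the nonresearch group

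*Protocol article*

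**What the plan says.** Objective 1 in Data Analysis (improving treatment selection) contains two expectations. The first is that clients enrolled later improve faster than those enrolled earlier, "as measured by instruments in Table 1". The second depends on a waiver of consent: "we expect that research participants will show greater improvements in mental health than nonresearch participants when controlling for clinic intake date". The second sentence names no instrument.

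The Table 1 caption gives the mode of collection: "All instruments are administered at baseline, 6 months, and 12 months using the Innowell platform, except for the Outcome Rating Scale and Session Rating Scale". Those two scales are collected in REDCap after each session.

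Phase 3 states who enters the platform: "new clients who consent are onboarded to the Innowell platform". Objective 2 describes the comparison group as "those who opt out of research (and do not complete PROMs using the Innowell platform". Data Analysis adds that these clients are assigned to a stratum by clinical judgment, without PROM results.

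Phase 3 also describes the chart review that the waiver would extend to nonconsenting clients. Its purpose is to understand "the impact of implementing standardized PROMs and stratified care on the services clients use at the study clinic", together with use of the wider health system.

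**The concern.** A between-group comparison of improvement needs the same outcome, measured at least twice, in both groups. Here, not completing the platform's PROMs is part of what distinguishes the comparison group. A waiver gives access to records that already exist; it cannot supply scores that were never collected.

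Data Analysis says that longitudinal inference cannot control for other things changing over time, and it offers the research-versus-nonresearch comparison as more direct evidence. If the mental health part of that comparison has no outcome in one group, the analyst must either drop it or improvise a proxy from chart notes. Such a proxy would be set against standardized self-report in the other group, so a difference in measurement could pass for a difference in effect.

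**Working it through.** The article gives no figure to reproduce. The check is to trace each named data source and ask whether it yields a repeated symptom measure in each group.

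| Source | Research clients | Nonresearch clients |
|---|---|---|
| Innowell instruments (Table 1) | Baseline, 6 and 12 months, plus readministration at three-monthly reviews (Phases 1 and 3) | None: not onboarded (Phase 3), no PROMs completed there (Data Analysis, objective 2) |
| Outcome Rating Scale and Session Rating Scale in REDCap (Phase 1, Table 1) | After each session | Not stated; probably none |
| Chart review (Phase 3) | Services used, wider health system use | The same, under a waiver; no symptom score named |
| Clinic and regional administrative data (Table 3; objectives 2 and 3) | Acute psychiatric care, dropout, sessions, time in program, cost | The same, under a waiver; no symptom score named |
| Administrative variables for the consent-bias check (Potential Challenges and Limitations) | Demographics, diagnoses | The same; not a measure of change |

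Table 1 has 20 rows. Two of them, the Outcome Rating Scale and the Session Rating Scale, are collected in REDCap, so 20 − 2 = 18 rows come through Innowell. All 18 are unavailable for nonresearch clients at baseline and at follow-up. Of the other two, the Session Rating Scale measures satisfaction with a session and the Outcome Rating Scale measures overall well-being. Neither is a symptom-domain measure.

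The quantity that objective 1 would compare is

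D = (mean change in research clients) − (mean change in nonresearch clients),

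adjusted for intake date. The second term has no observations from any Innowell instrument. More clients add information to the first term only. Adjusting for intake date does not help, because it needs outcome values in both groups at comparable dates.

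The other planned analyses do not share the problem:
- **Time in treatment (objective 2) and average cost (objective 3):** both rest on administrative data that a waiver would open for both groups.
- **Early versus late enrolment (objective 1):** this uses research participants' own scores.

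**The case against.** The strongest reply is that the sentence on research versus nonresearch clients names no instrument. The reference to Table 1 closes the preceding sentence, on early versus late enrolment. A reader might infer that the article commits this contrast to Table 1 scores; on the text it does not. Table 3 lists acute psychiatric care and dropout, which could be obtained without PROMs, and a condensed article may leave outcome definitions to a fuller document. This stands in part. However, the article names no alternative measure of mental health improvement, and service use or dropout does not measure symptom change. It also says affirmatively that the comparison group lacks platform PROMs, which goes beyond leaving a detail out.

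Three other stronger readings are tempting but unsupported:
- **That all of Table 1 is missing for nonresearch clients.** This is secure for the Innowell instruments only. Phase 1 says that clients are sent the two session scales and does not restate a consent condition. Ethical Considerations places participant data in REDCap, which makes the study-only reading likely but not certain.
- **That the article says charts hold no outcome measures.** Principal Findings says of standard care, historically, that "treatment progress is not systematically tracked using objective measures for most clients". That describes past practice and does not mention charts. It makes a routine substitute unlikely but does not rule one out.
- **That this is the only between-group test.** Time in treatment and cost are also compared, and the remark about more direct evidence covers the comparison as a whole.

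The weight of the point is also limited. The stated aim is feasibility and acceptability, the evaluation is exploratory, and the expectation depends on a waiver not yet obtained. The waiver, if granted, would still not supply the missing outcome.

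**Conclusion.** The point holds for the comparison of symptom improvement between research and nonresearch clients. That contrast cannot be estimated from the data the article plans to collect, at any sample size, because one group has no repeated symptom measure in any named source.

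The conclusion assumes that charts and administrative records contain what the article describes and no routine symptom scores, and that the REDCap session scales go to study participants only. If the Outcome Rating Scale did reach every client and could be used under the waiver, overall well-being could be compared, but not the symptom domains. The article does not plan that use.

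The defect is confined to one conditional, non-primary expectation.

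**What to change.** Three changes of wording in Data Analysis:

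1. Remove the prediction of greater mental health improvement in research than in nonresearch clients, and state that symptom change is evaluated among research participants only.
2. Limit the research-versus-nonresearch contrast to outcomes recorded the same way in both groups and already in Table 3: psychiatric urgent care, emergency or hospital use over a fixed window from stratum assignment; treatment dropout; number of sessions; time in program; and cost. The article gives no window length, so the study team should set one before the comparison is run.
3. State that stratum changes are not a comparative outcome. PROM results inform them in research clients only, so they are partly a product of the process under evaluation.

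No new data collection is needed. The loss is one conditional, non-primary hypothesis. The change does not remove the difference between clients who consent and those who do not, which the article already acknowledges as a possible bias and plans to examine.
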